**Table 1: Outcomes Measured**

| Outcome of Interest                      | Source & Description                                                                                                                                                                                                                                                                                                                                                                                                                                                                                                                                |
|------------------------------------------|-----------------------------------------------------------------------------------------------------------------------------------------------------------------------------------------------------------------------------------------------------------------------------------------------------------------------------------------------------------------------------------------------------------------------------------------------------------------------------------------------------------------------------------------------------|
| Demographics and Other Basic Information | Developed by the study team. Includes questions that capture participating parent-child dyad data regarding race/ethnicity, age, and sex.                                                                                                                                                                                                                                                                                                                                                                                                           |
| Family Resilience and Connection         | To measure the parent-child relationship in the face of stress and adversity, we will use Bethell, et al.'s six-item scale assessing family resilience, parent-child connection, and parent coping. The four family resilience index items are adapted to include additional response options to capture greater nuance. In the original scale, there is only one checkbox response option provided ("all of the time.") In our questionnaire, we will include the additional response options of "Sometimes" and "None of the time."  |
| Family Health                            | The Family Health Scale developed by Crandall et al. was used to measure global family health. The survey includes four subscales: 1) family social and /emotional health processes, 2) family healthy lifestyle, 3) family health resources, and 4) family external social supports and a short form to measure global family health. Our study includes the validated 32-item long-form version of the FHS.                                                                                                                          |
| Parent and Child General Health          | This component of the survey will be included to ask the participating parent's views on their own as well as their child's general health. We will solely include the first item found on the validated SF-12 Health Survey to assess this construct. We ask the question twice, though we will adapt the second iteration to reference the index child's health.                                                                                                                                                                                  |
| Nutrition                                | To assess the index parent's food and drink intake, we will include the brief eight-item Starting The Conversation (STC) Scale developed by Paxton, et al.  This survey has been validated in previous literature and no adaptations will be made. To assess child nutrition, the longer, in-depth Child Dietary Screener developed by the Centers for Disease Control will be used.                                                                                                                                      |

|                                      |                                                                                                                                                                                                                                                                                                                                                                                                                                                                                                                     |
|--------------------------------------|---------------------------------------------------------------------------------------------------------------------------------------------------------------------------------------------------------------------------------------------------------------------------------------------------------------------------------------------------------------------------------------------------------------------------------------------------------------------------------------------------------------------|
| Sleep                                | The Pittsburgh Sleep Quality Index will be used to measure the participating parent's quality and patterns of sleep.  We will include 3 items of the original 24-item long survey. The survey has been previously tested and validated by other research studies. To assess the index child's quality and patterns of sleep, Owens et al.'s Children's Sleep Habits Questionnaire will be used. This psychometrically validated, 8-item survey will be included without any adaptations.  |
| Food Patterns, Habits, and Behaviors | We will gather information on the parent-child dyad's food patterns and behaviors by utilizing relevant questions from the updated 2015-2016 version of the National Health and Nutrition Examination Survey. Specifically, we will include survey items from the Flexible Consumer Behavior Survey. To measure this same construct, we will also include items from the CDC's Youth Physical Activity and Nutrition Survey.                                                                           |
| Household Food Security              | To assess financially based food insecurity and hunger, we will use a short form of the U.S. Department of Agriculture Household Food Security Scale that was developed by Blumberg, et al. This scale includes 6 of the 18 items that were a part of the original scale.                                                                                                                                                                                                                              |
| COVID-19 Impact                      | To understand the extent to which index parents and their children are exposed to the impact of the COVID-19 pandemic, we will include the COVID-19 Exposure and Family Impact Scale (CEFIS) developed by Kazak, et al. This scale has been tested and validated by previous research studies. Part 3 of the CEFIS will be excluded from our survey.                                                                                                                                                   |

### Process Measures:

Process measures will be recorded for each scheduled session of the health coaching intervention and will also include TKO recipes prepared, session duration, modules completed, goals set, progress on goals, and parent and child health coach session attendance. Health coaches will record process measures following each scheduled session, regardless of whether the session was successfully completed (i.e., parent-child dyad canceled, rescheduled, or did not show for the session).

Both the intervention and control condition will receive up to 12 weekly short (about 2-3 minutes) TKO videos. Recipe specific groceries will be delivered to participants' homes by a third-party grocery delivery company or will be available for pickup at a central location(s). Please reference Table 2 to see the recipes that will be provided as part of this intervention. These recipes reflect foods that can be purchased with SNAP and WIC and include tested meals and snacks that were developed and evaluated in person in Parks and Recreation after-school programming (Heerman W, Elsakary Y, Sommer E, Escarfuller J, Barkin S. Assessing the Scale and Spread of an Experiential Teaching Kitchen in After-School Programming Among School-Aged Children) through the long-standing Nashville Collaborative partnership (<https://www.childrenshospitalvanderbilt.org/program/nashville-collaborative>). Over more than a decade, we have developed and tested programs together to improve health and wellness and reduce childhood obesity in our community.

**Table 2. TKO Recipes and Associated Groceries**

| Number & Recipe | Associated Groceries to be Delivered |
|-----------------|--------------------------------------|
|-----------------|--------------------------------------|

|                                    |                                                                                                                                                                                                                                                                                                                                                                                                                                      |
|------------------------------------|--------------------------------------------------------------------------------------------------------------------------------------------------------------------------------------------------------------------------------------------------------------------------------------------------------------------------------------------------------------------------------------------------------------------------------------|
| 1. Banana Oatmeal Cookies          | 
 
• 2 medium bananas
 
• 1 container of raw oats
 
• 1 container of cinnamon
 
                                                                                                                                                                                                                                                                                           |
| 2. Fruit Kabobs                    | 
 
• 1 whole pineapple (or 2 cans of pineapple chunks in juice)
 
• 1 orange
 
• 1 bag of grapes
 
• 1 carton of strawberries
 
• 1 pack of wooden skewers
 
                                                                                                                                                                                                |
| 3. Spinach Balls                   | 
 
• 1 bag of spinach (frozen or fresh)
 
• 1 box of whole wheat saltines
 
• 1 bag of parmesan cheese
 
• 1 small carton of eggs
 
• 1 bottle of olive oil
 
• 1 container of garlic powder
 
                                                                                                                                                       |
| 4. Fruit Pizzas                    | 
 
• 1 bag of medium whole wheat tortillas (minimum 6)
 
• 1 large container of plain, nonfat, Greek yogurt
 
• 1 container of strawberries
 
• 1 bag of grapes
 
• 1 can of mandarin oranges canned in juice
 
• 1 can of pineapple canned in water
 
• 1 container of vanilla extract
 
• 1 jar of honey
 
• 1 orange
 
       |
| 5. Zucchini Pizza Boats            | 
 
• 6 whole zucchinis
 
• 1 clove of garlic
 
• 1 bag of part skim mozzarella
 
• 1 bag of parmesan cheese
 
• 1 container of oregano
 
• 1 container of basil
 
• 1 container of salt
 
• 1 container of pepper
 
• 1 bottle of white grape juice
 
• 1 lemon
 
• 1 small can of tomato paste (minimum 3 oz.)
 
 |
| 6. Blueberry Peach Oatmeal         | 
 
• 2 large peaches
 
• 1 pint of blueberries
 
                                                                                                                                                                                                                                                                                                                                 |
| 7. Cinnamon Roasted Sweet Potatoes | 
 
• 2 sweet potatoes
 
                                                                                                                                                                                                                                                                                                                                                                 |
| 8. Salad Bar with Dressing         | 
 
• 1 bottle of apple cider vinegar
 
• 1 bottle of low-sodium soy sauce
 
• 1 container of honey
 
• 1 container of ground ginger
 
• 1 bag of spinach
 
                                                                                                                                                                                                  |

|                                 |                                                                                                                                                                                                                                                                                                                                                                                                                          |
|---------------------------------|--------------------------------------------------------------------------------------------------------------------------------------------------------------------------------------------------------------------------------------------------------------------------------------------------------------------------------------------------------------------------------------------------------------------------|
|                                 | 
 
• 1 bag or head of Romain lettuce
 
• 1 cucumber
 
• 1 box of Cherry tomatoes
 
• 1 bell pepper
 
• 1 red onion
 
• 1 bag of shredded carrots
 
• 1 bag of low-fat cheese
 
• 1 can of black beans (no salt added)
 
• 1 apple
 
• 1 box of berries (such as raspberries, blueberries, or strawberries)
 
 |
| 9. Chicken Taco Burger          | 
 
• 3 packs (1 lb. each) of lean ground chicken
 
• 1 jalapeno
 
• 1 bunch of cilantro
 
• 2 limes
 
• 1 bunch of scallions
 
• 1 jar of minced garlic
 
• 1 red onion
 
• 1 package of whole wheat buns (minimum 6)
 
• 1 head of lettuce
 
• 1 large tomato
 
                                             |
| 10. Black Bean and Corn Salad   | 
 
• 2 cans of corn (no salt added)
 
• 1 large cucumber or 2 small cucumbers
 
• 1 bunch of chives
 
• 1 can of black beans (no salt added)
 
• 1 bag of corn tortillas (not chips)
 
• 1 container of cumin
 
                                                                                                                          |
| 11. Build Your Own Banana Split | 
 
• 5 large bananas
 
• 1 large container of Greek yogurt, plain, nonfat
 
• 1 container of blueberries
 
• 1 container of blackberries
 
• 1 container of raspberries
 
                                                                                                                                                                       |

Those randomized to the intervention condition will also receive a 12-weekly health coach via a virtual platform (such as Zoom, FaceTime, or What's App) to provide an adapted version of the previously tested Healthier Families program. Adaptations include shortening each session to 30 minutes and delivering the programming via a virtual platform. The health coach will provide the Healthier Families modules (refer to Table 3) either to individual child-parent pairs or with groups of parents (virtual group visit model). Participants will be encouraged to share pictures or videos of what they are learning and applying in their families related to the modules (e.g., recipes, cooking, physical activity). To do this, platforms such as Facebook might be used. If Facebook will be used in any form or fashion, it will be completely voluntary, and participants will be made aware that it is not a secure platform. This will be included in the consent and will be emphasized when the programming

begins as well. Any use of Zoom for participant participation will use a version of Zoom procured through Vanderbilt. This programming has been developed and evaluated in partnership with Parks and Recreation with over 600 parent-child dyads and has been shown to have a statistically significant effect on absolute BMI (Barkin SL, Heerman WJ, Sommer EC, Martin NC, Buchowski MS, Schlundt D, Po'e EK, Burgess LE, Escarfuller J, Pratt C, Truesdale KP, Stevens J. Effect of a Behavioral Intervention for Underserved Preschool-Age Children on Change in Body Mass Index: A Randomized Clinical Trial).

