**8. Randomization:**

Randomization will occur after obtaining informed consent as well as the completion of certain baseline data collected by the parent (i.e., the baseline survey). This process will be completed within a maximum of a 30-day period. Once successfully completed, randomization will occur. Within the first cohort of the trial, parent-child dyads will be grouped according to parent preferred language (English versus Spanish), resulting in two strata within each region. Dyads within the strata will be randomized to the intervention and control groups within each of the two regions for a total of up to 200 parent-child dyads. Participants will be randomized by an unblinded KSP. Participants will be told which group they were randomized to.

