**9. Statistical Analysis Plan:**

We will describe participant characteristics using mean (standard deviation [SD]) or frequency (percentage), as appropriate. Comparison of descriptive variables between the control group and intervention group will be performed using a chi-squared test for categorical variables and a 2-sample, independent t-test for continuous variables. We will test for changes between baseline and 12-week follow-up outcomes using paired t-tests for within group comparisons. We will test for changes between baseline and 12-week follow-up outcomes using 2-sample, independent t-tests for between-group comparisons of the intervention and control group. We will conduct Tobit regression models for scales in which there is a considerable degree of skewed data.

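### If intervention families are coached in groups or share coaches, the independence-based tests in Section 9 can understate the standard error, and nothing in the protocol allows for this

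*Protocol*

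**What the plan says.** **Who is coached, and how.** Protocol Section 6 (text after Table 2) confines coaching to one arm: "Those randomized to the intervention condition will also receive a 12-weekly health coach via a virtual platform". The modules may be given "either to individual child-parent pairs or with groups of parents (virtual group visit model"). No rule says which dyads get which format, how large a group is, or whether its membership stays fixed.

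**What both arms share.** Under Process Measures in Section 6, "Both the intervention and control condition will receive up to 12 weekly short (about 2-3 minutes) TKO videos", together with the recipe groceries. Controls have no coach and no group.

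**Coaches.** The same part states that "Health coaches will record process measures following each scheduled session". The plural shows more than one coach; number and caseload are not given. The process measures listed (recipes, duration, modules, goals, attendance) do not include group or coach identity.

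**Randomization.** Section 8 randomizes single dyads: "Dyads within the strata will be randomized to the intervention and control groups within each of the two regions". The ceiling on enrolment is 200 dyads.

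**Analysis.** Section 9 tests change from baseline to 12 weeks between arms "using 2-sample, independent t-tests for between-group comparisons of the intervention and control group" and within arms "using paired t-tests for within group comparisons". It adds Tobit regression for skewed scales. Neither clustering nor a coach or group effect is mentioned.

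**The concern.** Individual randomization followed by group or shared-coach delivery in one arm gives a partially nested design. Intervention dyads in the same group share sessions, peers and a coach for 12 weeks; controls share none of these. If that sharing makes their changes more alike, the mean change in the intervention arm varies more from trial to trial than the t-test assumes, because the test counts each dyad as a separate piece of information.

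The consequence would be a confidence interval for the added benefit of coaching that is too narrow and a test that rejects too often. The effect of a few good groups or one good coach could be read as an effect of the programme. The intervention-arm paired t-test and the Tobit models rest on the same independence assumption.

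This is not a detail left to a separate analysis plan: Section 9 names the tests, and they do not fit one of the delivery formats that Section 6 permits.

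**Working it through.** The protocol states no alpha, power, effect size, SD, allocation ratio, ICC, group size or caseload, so it has no figure to reproduce. What follows is a range under stated assumptions.

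**From the protocol:** coaching in the intervention arm only; group or individual format; more than one coach; at most 200 dyads; independent t-test on change.

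**Assumed:** 100 dyads per arm; two-sided 5% test; equal SDs; every intervention dyad in a cluster of size m (a group or a coach's caseload); ICC of change between 0 and 0.10.

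**Formulas**
- Design effect in the intervention arm: DE = 1 + (m − 1) × ICC. Control arm: 1.
- True SE divided by t-test SE: √((1 + DE)/2).
- True error rate of the nominal 5% test: 2 × (1 − Φ(1.96 / SE ratio)).

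**Worked case, m = 10, ICC = 0.05.** DE = 1 + 9 × 0.05 = 1.45. SE ratio = √(2.45/2) = √1.225 = 1.107. Error rate = 2 × (1 − Φ(1.96/1.107)) = 0.077. The 100 intervention dyads carry the information of 100/1.45 = 69.

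| m | ICC | DE | SE ratio | True error rate, formula | Simulated |
|---|---|---|---|---|---|
| 1 | any | 1.00 | 1.00 | 0.050 | about 0.05 |
| any | 0 | 1.00 | 1.00 | 0.050 | about 0.05 |
| 5 | 0.01 | 1.04 | 1.01 | 0.052 | 0.051 |
| 5 | 0.05 | 1.20 | 1.05 | 0.062 | 0.065 |
| 5 | 0.10 | 1.40 | 1.10 | 0.074 | 0.072 |
| 10 | 0.01 | 1.09 | 1.02 | 0.055 | 0.057 |
| 10 | 0.05 | 1.45 | 1.11 | 0.077 | 0.078 |
| 10 | 0.10 | 1.90 | 1.20 | 0.104 | 0.104 |
| 25 | 0.01 | 1.24 | 1.06 | 0.064 | 0.065 |
| 25 | 0.05 | 2.20 | 1.26 | 0.121 | 0.124 |

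The simulated column applies the planned t-test to 20,000 trials per cell with no mean difference between arms; it agrees with the formula throughout. An ICC of 0.10 with 25 dyads per coach would give a ratio of 1.48, but nothing in the protocol points to a coach effect that large, and the conclusion does not rest on it.

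**Intervention-arm paired t-test.** There is no control arm to dilute the effect, so the SE ratio is √DE: √1.20 = 1.10 (m = 5, ICC 0.05), √1.90 = 1.38 (m = 10, ICC 0.10), √2.20 = 1.48 (m = 25, ICC 0.05).

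**Interval width under a valid analysis.** With k clusters, the Satterthwaite degrees of freedom are (DE + 1)² / (DE²/(k − 1) + 1/99).
- 20 groups of 5, ICC 0.05: 2.2² / (1.44/19 + 1/99) = 56 df, critical value 2.00. Width relative to plan: 1.049 × 2.00/1.97 = 1.07.
- 10 groups of 10, ICC 0.05: 2.45² / (2.1025/9 + 1/99) = 24.6 df, critical value 2.06. Width: 1.107 × 2.06/1.97 = 1.16.
- 4 coaches with 25 dyads each, ICC 0.05: 3.2² / (4.84/3 + 1/99) = 6.3 df, critical value 2.42. Width: 1.265 × 2.42/1.97 = 1.55. At ICC 0: 2² / (1/3 + 1/99) = 11.6 df, critical value 2.19, width 1.11.

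**The case against.** A reader might infer that the standard errors are too small and that the type I error exceeds 5%. The protocol does not support so flat a statement.

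- **Groups are only permitted.** Nothing says that they were used, for how many dyads, or with stable membership. The session log of goals and attendance reads naturally as a dyad-level record. This stands, so the point has to be conditional.
- **Shared coaches are an inference.** It rests on the plural and on the size of the trial. One coach per dyad for up to 100 dyads is implausible, but the caseload is unknown.
- **The understatement needs an ICC above zero.** At m = 5 and ICC 0.01 it is 1%. A range that left out this end would mislead.
- **There may be an offset.** Section 8 stratifies by language (within the first cohort) and region, and the unstratified t-test ignores this, which tends to make its standard error too large. If groups were formed by language or region, part of the within-group correlation would be a stratum effect that is balanced across arms. The size of this is unknown, and an unplanned offset is no reason to keep the method.
- **Timing.** Section 4 plans recruitment from February to May 2021, and Section 13 records registration in April 2022. New data fields may come too late, so the identifiers may have to be rebuilt from session records.

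None of this reconciles a permitted group format with tests that assume independence.

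**Conclusion.** The point holds in conditional form. If intervention dyads are coached in groups or share coaches, and their changes correlate within those clusters, the between-arm t-tests, the intervention-arm paired t-test and the Tobit models understate the standard error.

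For the between-arm test the factor runs from 1.00 (individual delivery with no coach effect, or ICC 0), through 1.05 to 1.20 (groups of 5 to 10, ICC 0.05 to 0.10; true error rate about 6% to 10%), to about 1.26 (25 dyads per coach, ICC 0.05; about 12%). This rests on 100 dyads per arm, equal SDs, all intervention dyads clustered and a two-sided 5% test, none of which the protocol states. The ignored strata may reduce it. How far the trial is affected cannot be settled until the delivery format and caseloads are known.

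**What to change.** 1. Record the delivery mode, group ID and coach ID for each intervention dyad, or reconstruct them from session records if delivery is over.
2. For dyads coached in groups, replace the between-arm t-test with a partially nested mixed model for change: a random group effect in the intervention arm only, controls as singletons, arm-specific residual variances, and Satterthwaite or Kenward-Roger degrees of freedom. Take the intervention-arm mean change from the same model in place of the paired t-test.
3. For the Tobit models, use cluster-robust variance with a small-sample correction.
4. If all delivery is individual and coaches are few, report the coach-clustered analysis as a sensitivity analysis, because a variance estimated from a handful of coaches is unstable.

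Section 9 names no covariates, and this change does not depend on adding any.

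**Cost.** Three fields per intervention dyad and revised analysis wording. Intervals widen modestly with many small groups (about 7% for groups of 5 and 16% for groups of 10, at ICC 0.05). With few coaches the price can be high: for four coaches, about 11% wider even at ICC 0 and about 55% wider at ICC 0.05.
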